### Eligibility Criteria

The eligibility criteria for patient recruitment is shown in Textbox 1.

Inclusion and exclusion criteria for patient recruitment.Inclusion Criteria:Admitted into the emergency department.Age 18-65 years.Sepsis with a quick Sequential Organ Failure Assessment (qSOFA) score≥2 [3,14,28,33]Consent by the patient or legal guardian.Exclusion Criteria:Mechanical ventilation at screening.Unconsciousness when admitted to emergency department (with Glasgow Coma Scale score<8)Preexisting pulmonary pathology as assessed by clinical symptoms or radiographic evidence in chest x-ray or by pulmonary bedside ultrasound (>2 B lines, a comet-tail artifact)History of pulmonary disorders (chronic obstructive pulmonary disease, asthma, parenchymal lung disease, or edema) or procedures.Preexisting cardiac pathology, disease, or dysfunction (ejection fraction<50, New York Health Association class>2) lung, or cardiac surgical procedures.History of liver cirrhosis, cancer, autoimmune disease, or immunosuppression.Patients under palliative care and patients facing imminent and inevitable death in the next 30 days due to causes other than sepsisSevere burns.Advanced kidney disease (chronic kidney disease stage 4 or above)Unstable medical conditions (eg, uncontrolled diabetes, uncompensated cardiac issues, heart failure, or chronic obstructive pulmonary disease).PregnancyWith other reasons or diseases needing a restricted fluid administration

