### Randomization and Blinding

Randomization will be web-based across centers using simple randomization stratified for patient’s age and center, with 1:1 allocation. The sequence will be confidential and will be managed by a researcher independent of patient treatment. The treating physician will use the web-based randomization service—Viedoc (PCG Solutions AB). To increase the internal validity, possible confounders, such as pulmonary disorders, mechanical ventilation affecting imaging findings and bias results, kidney disease, and pre-existing cardiac disorders will be excluded by strictly implementing the eligibility criteria (Figure 1, Textbox 1, and Multimedia Appendix 2).

Patients and physicians will be unblinded to avoid endangering the patient's health and life in the situation of an emergency. However other study investigators collecting data, drawing blood samples for the analysis of PaO_2_/FiO_2_ and other parameters, and documenting, entering, or analyzing data will be blinded. Allocation concealment will be maintained until all data is collected and analyzed for the blinded personnel. The treating physician and patients will be instructed not to disclose information to the independent assessor and the data analyst. All breaches of blinding will need to be reported and documented.

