### Outcomes

The primary outcome is the oxygenation (measured as mean PaO_2_/FiO_2_) at 48 hours after IV fluid administration. We expect a higher mean of PaO_2_/FiO_2_ in the intervention arm, which will be considered beneficial. A lower PaO_2_/FiO_2_ ratio is a sign of oxygenation compromise, which can occur with excessive fluid administration and increased EVLW. We will use PaO_2_/FiO_2_ ratio because it is a reliable and commonly used index of oxygenation that is easy to obtain and clinically significant as a predictor for mortality in patients with sepsis [26,35]. Arterial blood samples will be obtained for PaO_2_ measurement. FiO_2_ will be estimated based on widely accepted approximated values for those patients not mechanically ventilated [36].

The secondary outcomes will be assessed at time points of 0, 6, 12, 24, and 48 hours and after 15mL/kg of fluid administration, and also at 30 days. We will then evaluate (1) means of PaO_2_/FiO_2_ ratio between groups at these time points, (2) the incidence of pulmonary outcomes (pulmonary edema, acute respiratory distress syndrome, or need for invasive mechanical ventilation), (3) mean SOFA score, (4) mean creatinine level (in milligram per deciliter), (5) mean amount of volume of administered fluid, and (6) proportion frequency of 30-day mortality. Additionally, the type of IV fluid will be documented (Table 1).

Pulmonary outcomes (namely, pulmonary edema) will be confirmed by physicians based on symptoms and signs (eg, shortness of breath after fluid resuscitation and crackles), laboratory parameters (raised NT-proBNP, adjusted for age [37]), and x-ray findings suggestive of pulmonary edema.

The outcomes will be measured and documented in data collection forms by a nurse from the participating center. These forms will be made available in the protocol. Reliability and validity of laboratory tests at different participating centers will be made available in the protocol.

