### Sample Size Justification

The sample size considerations were based on the PaO_2_/FiO_2_ differences between groups obtained from comparable prospective studies [26,39,40], where EVLW indices were used as a predictor for mortality. A PaO_2_/FiO_2_ ratio difference (delta) of 48 mm Hg was detected between the groups of survivors (mean 150, SD 81) and nonsurvivors (mean 198, SD78). Based on these studies, a delta of 25 mm Hg between the groups was considered clinically meaningful and feasible for our study. Interim analysis for safety reasons will be performed after 50% (170/ 340) of patient recruitment. An independent blinded statistician would perform the interim analysis and report to the data safety monitoring committee, as only safety is the monitored outcome no alpha level modification is needed (Multimedia Appendix 4 Interim analysis and safety).

The sample size was calculated (*α*=.05; ß=.80) with a potential dropout rate of 5% (17/340), resulting in n=170 patients per arm in a total of N=340 patients (Figure 1).

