### Statistical Analysis

The primary outcome will be PaO_2_/FiO_2_, a continuous variable. Mean (SD) will be reported after testing for normality, and then will be analyzed via *t* test. For secondary outcomes, a repeated measure ANOVA and *t* test will be used for analysis of continuous data. Categorical data will be reported using proportions and will be analyzed using chi-square test.

All analysis will be conducted according to the principle of intention-to-treat, and multiple imputation technique will be used to account for missing data. A subgroup analysis will be performed based on randomization of age, site, and severity of sepsis. An intention-to-treat analysis approach will be used in this study (Multimedia Appendix 4 Missing Data).

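### The chi-square test for 30-day mortality and pulmonary outcomes does not use the age and centre strata of the randomisation, and loses power if those strata predict the outcome

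*Protocol article*

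**What the plan says.** - **Test.** Methods, Statistical Analysis: "Categorical data will be reported using proportions and will be analyzed using chi-square test". No stratification or adjustment is mentioned.
- **Outcomes affected.** Methods, Outcomes lists among the secondary outcomes the incidence of pulmonary events and the "proportion frequency of 30-day mortality".
- **Randomisation.** Methods, Randomization and Blinding: web-based, "using simple randomization stratified for patient’s age and center, with 1:1 allocation". Neither blocks nor minimisation is mentioned.
- **Use of the strata in the analysis.** Only this: "A subgroup analysis will be performed based on randomization of age, site, and severity of sepsis".
- **Size of the trial.** It is derived from PaO2/FiO2 alone, "with a potential dropout rate of 5% (17/340), resulting in n=170 patients per arm in a total of N=340 patients". The article gives no event rate or power for the binary outcomes, no age cut-point and no number of centres.

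**The concern.** Factors chosen for stratification are usually chosen because they are expected to predict outcome. Centre could do so here: after the initial control bolus, fluid type and rate follow local practice, and physicians confirm pulmonary edema partly from symptoms and signs. A test that ignores such factors leaves between-stratum variation in its variance estimate and does not correct for chance imbalance between arms within strata. The subgroup analysis asks whether the effect differs between strata; it does not sharpen the overall comparison. At stake is some power on the clinical outcomes that stand beside a surrogate primary outcome, in a trial not sized for them.

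**Working it through.** **1. The plan's own figure.** No figure is given for the binary outcomes, so the check starts from the stated 170 per arm. Inputs from Sample Size Justification: difference 25 mm Hg, SDs 81 and 78 (mean 79.5), alpha 0.05 taken as two-sided, power 0.80, dropout 5%.

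n per arm = 2 × (1.960 + 0.842)² × SD² / 25²

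- SD 79.5: 15.70 × 6320.25 / 625 = 158.7, so 159; 159 / 0.95 gives 168.
- SD 81: 15.70 × 6561 / 625 = 164.8, so 165; 165 / 0.95 gives 174.

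The stated 170 is reproduced to within 3%, so N = 340 is used below.

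**2. The two tests.** With event proportions p1 and p0, arm sizes n1 and n0, and pooled proportion p:

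- Chi-square (Pearson, no continuity correction): (p1 − p0)² / [p(1 − p)(1/n1 + 1/n0)].
- Cochran-Mantel-Haenszel (CMH): [Σ(x1s − n1s·ms/ns)]² / Σ[n1s·n0s·ms(ns − ms) / (ns²(ns − 1))], where, in stratum s, x1s is events in the treated arm, ms all events, and n1s, n0s and ns the two arm sizes and the total.

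The pooled p(1 − p) contains the variance of risk between strata. The CMH variance does not.

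**3. Assumptions not in the article.** Eight equally likely strata (4 centres × 2 age groups); mean control risk 20% or 30%; odds ratio 0.5 for power; between-stratum SD of 0, 0.5, 1.0 or 1.5 on the logit scale. Allocation within strata is either simple or in permuted blocks of 4. There were 100,000 null and 50,000 alternative runs per setting. The Monte Carlo standard error is about 0.07 points for a rejection rate near 5% and 0.2 points for a power near 65%.

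Four centres is plausible. Recruitment and Adherence implies 50 to 100 patients per centre per year over 12 to 18 months, so 50 to 150 per centre. That gives 340/150 = 2.3 to 340/50 = 6.8, or about 3 to 7 centres.

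**4. Type I error of the chi-square test (nominal 5%)**

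| Logit SD | Simple within strata | Blocks of 4 |
|---|---|---|
| 0 | 5.0% | 5.0–5.1% |
| 0.5 | 5.1% | 4.4–4.6% |
| 1.0 | 5.0% | 3.3–3.6% |
| 1.5 | 5.0–5.1% | 2.1–2.4% |

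CMH stays at 4.9–5.1% throughout. With a continuity correction the chi-square rejects at 3.6–3.8% under simple allocation whatever the spread. That comes from the correction and not from the strata.

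**5. Power, chi-square v CMH**

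| Mean control risk | Logit SD (range of stratum risks) | Simple | Blocks of 4 |
|---|---|---|---|
| 20% | 0 | 62.6 v 61.5 | 63.2 v 62.9 |
| 20% | 0.5 (9–35%) | 60.2 v 60.4 | 60.1 v 61.1 |
| 20% | 1.0 (3–50%) | 53.7 v 57.8 | 53.9 v 58.3 |
| 20% | 1.5 (1–63%) | 45.0 v 53.3 | 44.8 v 54.7 |
| 30% | 0 | 76.8 v 75.8 | 76.8 v 76.6 |
| 30% | 0.5 (15–48%) | 73.7 v 74.5 | 74.0 v 75.2 |
| 30% | 1.0 (6–65%) | 64.3 v 70.1 | 65.6 v 71.1 |
| 30% | 1.5 (2–78%) | 51.8 v 64.1 | 52.7 v 65.4 |

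The change from stratifying is −1.1 to −0.2 points at SD 0, +0.2 to +1.2 at SD 0.5, +4.1 to +5.8 at SD 1.0, and about +8 to +13 at SD 1.5.

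**6. Cross-check.** A separate simulation used 10 strata of 34 patients, odds ratio 0.5 and 40,000 runs per setting. Under simple allocation it gave 66.3% v 65.8% when control risk ran from 12% to 34%, 64.3% v 67.8% for 5% to 55%, and 60.9% v 68.6% for 3% to 70%. The pattern is the same.

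**7. Effect measure.** A constant odds ratio does not give a constant risk difference. With odds ratio 0.5, a control risk of 5% falls to 2.6% (−2.4 points) and one of 55% falls to 37.9% (−17.1 points).

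**The case against.** **The plain test is valid and the article is condensed.** It does not say unstratified, and a stratified version could be specified in an analysis plan that is not shown. Part of this stands: under the allocation as worded the test keeps its level. But the article names a test and gives the strata a different role (subgroups), so the text as it stands reads as a choice.

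**The larger gains need spreads that the article gives little reason to expect.** Eligibility is limited to "Age 18-65 years" and excludes ventilated patients and many major comorbidities. Centres must be academic hospitals with an ICU, high sepsis volume and standardised protocols. This stands: it makes strong prediction by age and centre less certain, though it does not rule it out.

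**Stakes.** A reader might infer that the phase III decision is weakened. The article does not support that. The Limitations section leaves hard clinical outcomes to phase III, and the Discussion makes phase III follow positive results without naming mortality as the deciding evidence. No power was promised for these outcomes, and neither test reaches 80% in any setting above.

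**Conclusion.** The point holds as a conditional loss of efficiency. The article randomises "stratified for patient’s age and center, with 1:1 allocation" and then names a test for the categorical outcomes that does not use these factors. The cost is 0.2 to 1.2 points of power at moderate spread and 4.1 to 5.8 at strong spread. If the strata carry no prognostic information, stratifying costs 0.2 to 1.1 points. These sizes rest on the assumed event rates, odds ratio, number of strata and spread.

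Two stronger readings are not supported. A reader might infer that the chi-square test is conservative in this trial. That needs balance within strata, for example by blocks, whereas the article says simple randomisation, under which the level stays at 5%. A reader might also infer that power is lost in every case. It is not: with weakly prognostic strata the two tests differ by about a point or less, in either direction.

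The matter is confined to secondary outcomes and does not affect the primary conclusion.

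**What to change.** Amend the sentence on categorical data in Statistical Analysis:

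- Compare binary outcomes with a Cochran-Mantel-Haenszel test stratified by centre and age group, or with a logistic model containing both factors. The stratified test held its level under both allocation schemes examined.
- Merge small centres by a rule fixed before unblinding.
- Report a Mantel-Haenszel odds ratio with a 95% CI. Alternatively, report a stratum-weighted average risk difference with a 95% CI, described as an average and not as a common difference. Show crude proportions descriptively.

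Cost: a few lines of text and no new data. By the article's own account the centres are still being selected and the protocol is not yet registered, so the change is easy now. The downsides are the need for a sparse-stratum rule and the possibility that the gain is nil or slightly negative.

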### Limitations and Contingency Planning

Our study might lead to promising results but is not without limitations. The use of surrogate markers can be seen as a limitation. Using a surrogate marker to ensure study feasibility is universal in phase 2 trials. We will plan to study hard clinical outcomes in the following phase III trial. The chosen surrogate variable of PaO_2_/FiO_2_ ratio is a central component of the SOFA score [27,41]. Higher SOFA scores are associated with higher mortality [29]. Lower PaO_2_/FiO_2_ ratio is associated with adverse outcomes in patients with sepsis [41]. Additionally, the SOFA score will be assessed to evaluate changes in the patient’s status over time since it is a core component of Sepsis-3 guidelines [14,28] and has predictive value [42]. It represents a valuable additional surrogate variable. These surrogate variables will be supplemented by other variables essential for evaluating the progress of sepsis.

We have strict inclusion and exclusion criteria in order to enhance the detectability of differences between groups and show the efficacy of the intervention if present. However, this may limit the external validity of our results and slow down the recruitment process. (Multimedia Appendix 4 Contingency Planning).

Ultrasound is an operator-dependent intervention. To standardize the ultrasound technique and interpretation, trained physicians who prove competent will perform the ultrasound. Kappa statistics will be used to assess inter-rater reliability.

## Results

The study funding and ethical approval are being acquired, and the participating centers are being selected. The protocol will be registered with the intended registry name “Fluid administration in Emergency Room limited by Lung Ultrasound (FERLU) in patients with sepsis [31]: a phase II multicenter randomized controlled trial.” The protocol will follow the SPIRIT checklist (Multimedia Appendix 3) [43] and include all items from the World Health Organization Trial Registration Data Set. Details of sponsorship, complete protocol, and model consent forms will be provided. Changes will be regularly updated. The study is planned to be performed from 2021 to 2022, with enrollment starting in 2021. First results are expected in 2022. Based on the results of this study, independent recommendations will be made for potential further clinical trials and their designs. The results will be disseminated at international meetings in the fields of emergency medicine and intensive care and published in a peer-reviewed journal. The study will follow the authorship criteria of the International Committee of Medical Journal Editors for all publications.

## Discussion

The protocol and subsequent results can be the basis for an improved and individualized therapy regimen for initial sepsis treatment, which avoids damage resulting from excess fluid. It will be a further step toward new guidelines on tailored therapy approach for fluid administration in the management of sepsis.

Sepsis is one of the main reasons for ICU admissions, and 6%-30% of all ICU patients are assumed to suffer from sepsis [44]. The disease is associated with a high mortality and a considerable cost burden [45-47]. The adequate initial volume application is essential in the initial resuscitation of sepsis [8-11], and it affects patients’ outcome and mortality risk [4-6]. There is a need for individualized fluid resuscitation of patients with sepsis and septic shock at emergency departments [8-11]. Therefore, there is a need for reliable, fast, and easily applicable screening tools and protocols to individualize the fluid amount for every patient. This approach could be also embedded as a telemedicine expert consultation to save resources [48]. Lung ultrasound following the FALLS-protocol could be a feasible and aiding approach [22,24].

Lung ultrasound as per the FALLS-protocol is not well validated yet. Therefore, our proposed trial, as a first randomized clinical trial, will lay the ground for developing and validating the bedside lung ultrasound protocol for detecting EVLW as a tool guiding early treatment in the emergency department and help to validate the FALLS-protocol usage in emergency departments.

In this phase II multicenter parallel-group superiority trial, we will guide the fluids using bedside lung ultrasound in patients with sepsis evaluated by B lines as a marker for EVLW. Based on previous literature, it is hypothesized that patients receiving individually-adapted fluid therapy limited by lung ultrasound have better oxygenation leading to a better outcome and lower risk of mortality. With positive results, the study would proceed to a phase III with more liberal inclusion and exclusion criteria mimicking a real-life scenario. FERLU trial will lead to a deeper understanding of the fluid response in sepsis. The results of this study could help to decrease the mortality in this high-risk group of patients with sepsis by providing physicians an additional tool applicable in the emergency.

## Appendix

Multimedia Appendix 1 FERLU research question in PICOT format.

Multimedia Appendix 2 Template for an attrition diagram.

Multimedia Appendix 3 SPIRIT-compliant checklist for the FERLU trial.

Multimedia Appendix 4 Supplemental information.

## Abbreviations

ARISE: Australasian Resuscitation in Sepsis Evaluation
BLUE: Bedside Lung Ultrasound in Emergency
CONSORT: Consolidated Standards of Reporting Trials
EVLW: extra vascular lung water
FALLS: Fluid Administration Limited by Lung Sonography
FERLU: Fluid administration in Emergency Room limited by Lung Ultrasound FiO2: fraction of inspired oxygen
ICU: intensive care unit
IV: intravenous
PaO2: partial pressure of arterial oxygen
PICOT: Population, Intervention, Control, Outcome, and Time
ProCESS: Protocolized Care for Early Septic Shock
ProMISe: Protocolised Management in Sepsis
qSOFA: quick Sequential Organ Failure Assessment
SOFA: Sequential Organ Failure Assessment
SPIRIT: Standard Protocol Items: Recommendations for Interventional Trials
